### Adverse events monitoring

Adverse events will be monitored using adverse event forms. All adverse events will be discussed with the principal investigator and the study team to see whether any adaptations to the protocol or program should be made as a result of the adverse event and to insure safety for all participants.

### Data management

Data will be entered ongoing over the study period. Data will be securely stored in a locked cabinet and in a secured online database. Random data checks will be performed to promote data quality.

### Statistical analysis

#### Effects of CCT

The primary and secondary outcomes will be analyzed using an identical analytic model, which will follow the intention-to-treat principle, such that all randomized participants will be included to estimate treatment effects irrespective of deviations from treatment protocol (e.g., loss to follow-up, non-compliance). This will be done using linear mixed models using maximum likelihood estimation. The model will include random intercepts, and fixed effects of time (baseline, trial completion), intervention assignment (FBT, Ex-FBT, BAT), and their interaction. Baseline MoCA score and age will also be included as fixed effect covariates. Treatment effects will be indicated by a statistically significant treatment by time interaction. Two planned simple contrasts will be performed to assess differences in changes in the primary and secondary outcomes between: 1) the FBT group and the BAT group; and 2) the ex-FBT group and the BAT group. A secondary planned contrast will determine whether FBT and ex-FBT will differ in changes in the primary and secondary outcomes over time. To explore maintenance of treatment effects, we will perform repeated measures with linear mixed models using maximum likelihood estimation. The models will include random intercepts, and fixed effects of time (baseline, trial completion, 1-year follow up), intervention assignment, and their interaction. Baseline MoCA score and age will also be included as fixed effect covariates.

Follow-up sensitivity analyses will restrict the study sample to individuals with valid data at all three time points (baseline, trial completion, and 1-year follow-up). The same linear mixed models describe above will be employed to determine whether inferences will be similar for the intention-to-treat and complete-case study samples.

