#### Primary outcome: Episodic memory

Our primary cognitive outcome will be (verbal) episodic memory as measured by the Rey Auditory Verbal Learning Test (RAVLT) [38]. The RAVLT is a valid, reliable, and widely used instrument of (verbal) episodic memory. Notably, a 2013 prospective study showed that among a combination of neuropsychological, neuroimaging, and cerebrospinal fluid markers, RAVLT performance was the best individual predictor of MCI conversion to dementia [39]. For the RAVLT, a list of 15 common words (List A) will be read to participants five times. Immediately after each time, they will be asked to recall as many words as possible. After the fifth trial, an interference list (List B) will be presented, after which participants will be asked to spontaneously recall the words form the original list (List A). Then, participants will be asked to spontaneously recall the original words (List A) after a 20-min delay (i.e., long delay free recall), and finally, they will be asked to circle words from the original list (List A) in a paragraph of text containing thirty underlined words (i.e., words from the original list plus distractor words). Scores will be calculated as the total number of words recalled: 1) across the five trials (total acquisition); 2) after the interference list (recall after interference); 3) on the fifth trial minus after the interference (loss after interference); 4) at recognition (number of words correctly identified from list A); and 5) after the 20-min delay (long delay free recall – our primary RAVLT measure of interest). We will focus on changes in memory (trial completion minus baseline) over the course of the study.

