### Sample size and randomization

The required sample size for this study is calculated based on changes in the RAVLT (retention score). Specifically, we predict a mean change of 0.31 for the FBT group, a mean change of 0.40 for the Ex-FBT group, and a mean change of −0.31 for the BAT group. We made these estimates based on the work of Diamond and colleagues [58]. With a pooled standard deviation of 1.1, and alpha of 0.05, we will need 36 participants for a power of 0.80. To accommodate for a 10% drop-out rate, our total sample size comes to 120 participants (i.e., 40 FBT, 40 Ex-FBT, and 40 BAT).

Participants will be randomly allocated (1:1:1) to FBT, Ex-FBT, or BAT. The randomization sequence will be generated by an independent member of the team using computer software (www.randomization.com). Blocked randomization will be used, with a block size of 12. The group allocation will be concealed for the study coordinator. After enrolment, performed by a research assistant, and completion of the baseline assessment, the study coordinator will send a list of participant identification numbers to the independent member responsible for the randomization. This independent member will provide the study coordinator with the group assignment for the enrolled participants. After completion of baseline assessment at VGH, the participants will be informed of their group assignment. Outcome assessors will be blinded after treatment allocation.

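### The primary mixed model amounts to an unadjusted comparison of mean change: MoCA and age cancel from the treatment contrast and baseline RAVLT is not conditioned on, so precision is lost, though validity is not

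*Protocol article*

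**What the plan says.** The primary measure is RAVLT recall "after the 20-min delay (long delay free recall – our primary RAVLT measure of interest", and the target is stated on the change scale: "We will focus on changes in memory (trial completion minus baseline) over the course of the study" (Protocol article, Primary outcome: Episodic memory).

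Under Statistical analysis, Effects of CCT, the model is written out for the primary and all secondary outcomes: "The model will include random intercepts, and fixed effects of time (baseline, trial completion), intervention assignment (FBT, Ex-FBT, BAT), and their interaction". Then: "Baseline MoCA score and age will also be included as fixed effect covariates". The test is fixed as well: "Treatment effects will be indicated by a statistically significant treatment by time interaction". The contrasts of FBT and Ex-FBT with BAT are described in the same terms: "Two planned simple contrasts will be performed to assess differences in changes in the primary and secondary outcomes between". Estimation is by maximum likelihood, and all randomised participants are included.

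The section states no covariate-by-time term, no baseline RAVLT covariate and no common-baseline constraint.

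**The concern.** A reader of this section would take the treatment effect to be adjusted for MoCA and age. In the model as written, both are constant within a person and enter only as main effects, whereas the treatment effect is a within-person contrast. They therefore shift a participant's level at both visits and leave the change untouched.

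The baseline variable likely to matter most for precision, baseline RAVLT, sits in the response vector with a separate mean for each arm. A chance difference between arms at baseline then carries fully into the difference in change, instead of being discounted according to how strongly baseline predicts follow-up.

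At stake is precision that could be had from data the trial already collects. Because one identical model serves every outcome, the loss recurs in each secondary analysis.

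**Working it through.** **Inputs from the protocol (Sample size and randomization).** The predicted changes are 0.31 (FBT), 0.40 (Ex-FBT) and −0.31 (BAT). The differences are 0.31 + 0.31 = 0.62 (FBT vs BAT) and 0.40 + 0.31 = 0.71 (Ex-FBT vs BAT). Pooled SD 1.1, alpha 0.05, 36 participants for power 0.80, 10% dropout, 120 in total.

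**Assumptions.** The 1.1 is the SD of change, 36 is per arm, and alpha is two-sided; the text states none of these outright. The pre-post correlation rho is not given, so a range is shown. Variances are taken as equal at the two visits, as the random-intercept model itself implies.

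**The plan's own figure.** The dropout step reproduces: 36/0.9 = 40 per arm, and 3 × 40 = 120. Two-sample t-test power at 36 per arm is 65.5% for a difference of 0.62 and 77.1% for 0.71. The normal approximation gives 66.7% and 78.2%, with 50 and 38 per arm needed for 80%. So 0.80 is approached for Ex-FBT vs BAT but not for FBT vs BAT. These figures serve here only as the starting point.

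**Why the covariates cancel.** For participant i in arm k:

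- baseline score = m + a_k + b1·MoCA_i + b2·age_i + u_i + error
- 8-week score = m + a_k + t + d_k + b1·MoCA_i + b2·age_i + u_i + error

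Subtracting gives change = t + d_k + difference of errors. The terms a_k, MoCA, age and u_i are all gone, and d_k is the treatment-by-time term. With complete pairs its estimate is the difference in mean change.

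**Check by simulation** (36 per arm; MoCA and age explaining 25% of between-person variance).

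- Complete data: the FBT vs BAT interaction estimate was 0.26095 with covariates, 0.26095 without, and 0.26095 as the raw difference in mean change. The SE was 0.2384 with covariates, 0.2385 without, and 0.2384 for the change score on the same maximum-likelihood scale. Over 300 replicates at each of four values of rho (0.5 to 0.8), model and change-score estimates did not differ.
- One data set with 10% missing at trial completion: SE 0.2455 with covariates and 0.2460 without; estimate 0.727 and 0.715. The SE was 0.235 with ANCOVA on completers. With a common-baseline model (random intercept) it was 0.227 without covariates and 0.222 with them as main effects.

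**Size of the loss.** Let s² be the variance at each visit.

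- Variance of change: 2(1 − rho)s²
- Residual variance given baseline: (1 − rho²)s²
- Ratio: (1 − rho²) / [2(1 − rho)] = (1 + rho)/2

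The residual SD is 1.1 × √((1+rho)/2). The last column is the cross-sectional SD implied by an SD of change of 1.1, that is 1.1/√(2(1 − rho)).

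| rho | variance ratio | reduction | residual SD | power, FBT vs BAT | power, Ex-FBT vs BAT | implied SD at one visit |
|---|---|---|---|---|---|---|
| as planned | 1 | – | 1.100 | 65.5% | 77.1% | – |
| 0.5 | 0.75 | 25% | 0.953 | 77.7% | 87.7% | 1.10 |
| 0.7 | 0.85 | 15% | 1.014 | 72.5% | 83.4% | 1.42 |
| 0.8 | 0.90 | 10% | 1.044 | 70.1% | 81.2% | 1.74 |
| 0.85 | 0.925 | 7.5% | 1.058 | 68.9% | 80.2% | 2.01 |
| 0.9 | 0.95 | 5% | 1.072 | 67.7% | 79.1% | 2.46 |

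(Two-sided t-test, 36 per arm. Any further gain from MoCA and age is not counted.)

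**The case against.** The strongest reply is that nothing here is an error. Under randomisation the difference in mean change is unbiased with correct type I error. The plan is also consistent with itself: outcome, sample size and contrasts are all on the change scale. That stands. A reader might infer that leaving chance baseline imbalance unadjusted biases the result or invalidates the test. The documents do not support this, because imbalance under random allocation adds variance, not bias.

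The second reply is about size, and it also stands. A reader might fix on the gain at rho 0.5 to 0.7, about 7 to 12 power points for FBT vs BAT. With an SD of change of 1.1, those correlations imply a spread at one visit of only 1.1 to 1.4 words. The test has 15 words, and the sample spans ages 65 to 85 and both probable MCI and normal cognition. A wider spread implies a higher rho: an SD of 2 gives about 0.85, with a gain of 3 to 4 points, and an SD of 3 gives about 0.93, with a gain of about 1.5 points (65.5% to 67.0%). The protocol cannot settle which applies.

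Third, it would be too strong to say that the stated covariates do nothing. Under dropout they enter through participants with one visit and may help support a missing-at-random assumption. In the simulated data set this changed the SE by 0.0005, so the contribution is small but not zero.

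Finally, the shortfall against the stated 0.80 power for FBT vs BAT is a separate sample-size question. It should not add weight to this point.

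**Conclusion.** The point holds as one of lost efficiency. As written, the primary treatment contrast is the unadjusted difference in mean change when pairs are complete, and nearly so in precision at 10% dropout. Baseline RAVLT is not used to sharpen it.

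The avoidable variance is 25% of the planned variance at rho 0.5, 10% at 0.8 and 5% at 0.9, and it vanishes as rho approaches 1. In power this is about 2 to 12 points for each contrast with BAT over rho 0.9 to 0.5. The cancellation follows from the model text and is certain. The size is not: it rests on an unstated correlation, equal variances at the two visits, and reading 1.1 as the SD of change. The change is worth making because it keeps the same treatment-effect target and uses only data already collected.

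**What to change.** Keep the likelihood-based mixed model, but constrain the arms to a common baseline mean: fit time and arm by post-baseline time, with no arm main effect, and use an unstructured covariance over visits. Enter MoCA and age with a by-time interaction so that they can act on the 8-week score. State the same model for the secondary outcomes. Participants with only a baseline value stay in, in line with the section's intention-to-treat aim.

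ANCOVA of the 8-week score on baseline score, MoCA, age and arm is a close complete-case alternative. It drops anyone without an 8-week score, so name it as a sensitivity analysis and not as an equivalent.

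The cost is a few sentences in the analysis plan and a small change in code, fixed before unblinded data are seen. No extra participants, visits or measurements are needed.

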#### Baseline cognitive status as a moderator

To determine whether treatment effects are similar for individuals identified as having MCI, we will add MCI status as an additional fixed effect in the linear mixed models described above. Moderation will be indicated by a statistically significant MCI status by treatment by time interaction. In the presence of moderation, the planned contrasts described above will be re-computed after stratifying by MCI status. This will identify how MCI status moderated the effects of treatment on the outcome of interest.

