The objective of the current proof-of-concept RCT will be to examine the effect of CCT, alone and preceded by a 15-min brisk walk, on cognitive function and to explore the underlying neural mechanism in community dwelling older adults. Therefore, our aim is four-fold: 1) To compare the effects of an 8-week CCT program (i.e., Fit Brains***®*** Training: FBT), as well as the effects of a 15-min brisk walk prior to FBT (i.e., Ex-FBT), with an active control (i.e., Balanced And Toned, BAT) on cognitive performance in older adults aged 65–85 years old; 2) Using structural and functional Magnetic Resonance Imaging (MRI), to explore the effect of FBT and Ex-FBT compared with BAT on brain structure and function; 3) To explore whether the effects of FBT and Ex-FBT are moderated by baseline cognitive status (i.e., Mild Cognitive Impairment (MCI) versus non-MCI); 4) To explore whether Ex-FBT has additional benefits compared with FBT; and 5) To explore whether potential benefits from CCT are maintained at 1-year follow-up.

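### The follow-up to the MCI interaction test compares arms within each stratum, which does not by itself show which programme's effect differs by MCI status

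*Protocol article*

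**What the plan says.** The section Baseline cognitive status as a moderator adds MCI status to the mixed model and sets one criterion: "Moderation will be indicated by a statistically significant MCI status by treatment by time interaction". It continues: "In the presence of moderation, the planned contrasts described above will be re-computed after stratifying by MCI status". The purpose of that second step is then given: "This will identify how MCI status moderated the effects of treatment on the outcome of interest".

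The contrasts in question come from the section Effects of CCT: "Two planned simple contrasts will be performed to assess differences in changes in the primary and secondary outcomes between" FBT and BAT, and Ex-FBT and BAT, with FBT against Ex-FBT as a secondary contrast. The Background words the matching aim as exploratory and about both programmes: "To explore whether the effects of FBT and Ex-FBT are moderated by baseline cognitive status".

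**The concern.** With three arms, two strata and two time points, the three-way interaction has (3 − 1) × (2 − 1) × (2 − 1) = 2 degrees of freedom. A significant result says that at least one arm difference varies with MCI status. It does not say whether FBT, Ex-FBT or both are responsible.

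The plan relies on the stratified contrasts for that answer. Each has as its null hypothesis that the effect in that stratum is zero. Moderation of a programme has a different null: that its effect is the same in both strata. None of the named contrasts addresses this second question. In strata of about 18 per arm, an identical effect can easily be significant in one stratum and not in the other.

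The arm-specific answer to the third aim is at stake. If only Ex-FBT is moderated, FBT could be reported as working in one cognitive group and not in the other. The Discussion foresees separate statements for healthy older adults and for those with MCI, so such a misattribution could reach the conclusions.

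**Working it through.** **Inputs from Sample size and randomization.** "we predict a mean change of 0.31 for the FBT group", "a mean change of 0.40 for the Ex-FBT group", and −0.31 for BAT; pooled SD 1.1; alpha 0.05; power 0.80; 36 participants; 10% drop-out; 120 in total, 40 per arm.
- FBT − BAT = 0.31 + 0.31 = 0.62.
- Ex-FBT − BAT = 0.40 + 0.31 = 0.71.

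**Assumptions.** The 36 is taken as per arm, since 36/0.9 = 40. Tests are two-sided. The SD is 1.1 in every cell, MCI shares are equal across arms, and change scores stand in for the mixed model without covariate gain. The document does not give the MCI share, so 30% to 70% is used.

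**The plan's own figure.** n per arm = 2(1.96 + 0.8416)² × 1.1² / difference² = 18.99 / difference².
- For 0.71: 18.99/0.504 gives 38 per arm; power at 36 is 0.78, close to the stated 36 and 0.80.
- For 0.62: 18.99/0.384 gives 50 per arm; power at 36 is 0.67.

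The stated size therefore roughly matches the Ex-FBT contrast in the whole sample. It makes no allowance for strata.

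**One stratum, equal split.** With 18 per arm, the standard error of FBT − BAT is 1.1 × √(2/18) = 0.367, and 0.62/0.367 = 1.69. Power is 0.39 by the normal approximation and 0.376 by the t test. If the effect is 0.62 in both strata, the chance of significance in exactly one is 2 × 0.376 × 0.624 = 0.47.

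**30/70 split.** With 11 and 25 per arm, power is 0.242 and 0.497. The chance of exactly one is 0.242 × 0.503 + 0.497 × 0.758 = 0.50.

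**After a significant interaction test.** Simulation of three arms by two strata, 200,000 trials per scenario. The two-degree-of-freedom interaction F test is applied at 0.05, then FBT − BAT is tested within each stratum, and separately as a direct between-stratum contrast. FBT − BAT is 0.62 in both strata, so any finding that FBT is moderated is false.

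| True Ex-FBT − BAT in the two strata | Split | Interaction test significant | FBT significant in exactly one stratum, given that | Direct FBT contrast rejects, given that |
|---|---|---|---|---|
| 1.42 and 0 (strong) | 50/50 | 0.80 | 0.49 | 0.06 |
| 1.42 and 0 | 30/70 or 70/30 | 0.73 | 0.52 | 0.07 |
| 0.71 and 0 (weak) | 50/50 | 0.27 | 0.57 | 0.15 |
| 0.71 and 0 | 30/70 or 70/30 | 0.23 | 0.59 | 0.16 |

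Without conditioning on the interaction test, the direct contrast rejects in 5%.

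**Sensitivity to the true FBT effect** (strong Ex-FBT moderation, after a significant interaction test, same splits). Significance in exactly one stratum occurs in about 11% if FBT − BAT is 0, 25% at 0.31, 49% to 52% at 0.62, and 20% to 33% at 1.2.

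**Joint probabilities, 50/50 split.** A significant interaction test together with a discordant FBT pattern: 0.80 × 0.49 = 0.39 under strong moderation; 0.27 × 0.57 = 0.15 under weak moderation.

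**The case against.** A reader might infer that the plan uses stratum-by-stratum significance to decide whether moderation exists, or that it will show false moderation about half the time. The text supports neither. Moderation is decided by an interaction test, which is a test of equality across strata. If no arm is moderated, that test is significant in only 5% of trials, and a discordant pattern for a given arm then has a joint probability of about 4%. The plan says contrasts are recalculated. It has no rule that significance in one stratum alone means moderation. Stratum estimates after a significant interaction are ordinary simple-effects follow-up, and comparing their sizes and intervals is a fair description of how the effect varies.

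Three further objections have weight:
- The Ex-FBT pattern of 1.42 and 0 is an invented scenario, with a peak at twice the protocol's 0.71.
- The three-way model already contains the two arm-specific interaction terms, and an analysis plan that is not shown may report them.
- The aim is exploratory, in a proof-of-concept trial, and the main contrasts are untouched.

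These points limit the size and severity. They do not remove the mismatch. The article names a procedure and says what it will identify, and that procedure does not compare strata. Its other decision rules are stated in terms of statistical significance, so reading the stratum contrasts the same way is a natural risk, though not a written instruction.

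**Conclusion.** The point holds in a limited form. The test for the existence of moderation is right. The sentence saying that stratified contrasts will identify how MCI status moderates the effects is not supported by those contrasts alone.

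The 49% to 60% error rate requires all of the following: stratum results read by significance, a true unmoderated FBT − BAT effect near 0.62 with SD 1.1 and 36 per arm, an MCI share between 30% and 70%, true moderation of Ex-FBT, and a significant interaction test. Outside those conditions it can be much lower, as the sensitivity figures show. It is not a property of the plan in general. Severity is low: this is a cheap improvement to an exploratory analysis, and the main treatment comparisons are not affected.

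**What to change.** In Baseline cognitive status as a moderator, make the identifying step two one-degree-of-freedom contrasts from the full three-way model, each with a 95% confidence interval: MCI by time by (FBT against BAT), and MCI by time by (Ex-FBT against BAT). Keep the stratum-specific contrasts as descriptive estimates with confidence intervals from the same model. Add that significance in one stratum and not in the other is not evidence that the programme is moderated.

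The cost is a sentence or two and two linear contrasts from a model already planned, with no extra data. There are two drawbacks:
- The intervals will be wide. At 18 per arm per stratum the standard error is 1.1 × √(4/18) = 0.52, so the 95% interval is about ±1.98 × 0.52 = ±1.03, wider than either predicted effect. Fewer arm-specific claims will be possible.
- The contrasts remain somewhat inflated by selection when reported only after a significant interaction test (about 6% to 7% or 15% to 16%, against a nominal 5%). They are better evidence on which programme is moderated, not error-free evidence.
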